### Recruitment and randomisation

Participant recruitment is taking place across a number of NHS Trusts across the North West, UK. Advertisements, including flyers and posters to promote the study are distributed throughout a range of NHS services. The trial also has a website to advertise the study (www.psych-sci.manchester.ac.uk/actissist/). In addition, researchers present verbal and written information outlining the study to health professionals. Potential participants are offered a participant information sheet along with an overview of the study by either a member of their care team or directly by the researcher. Eligible participants are identified by care co-ordinators and approached by a trained RA or clinical studies officers (CSO) from the UK Clinical Research Network (CRN). Participants deemed eligible to participate by the care co-ordinators are invited to take part and asked to provide informed consent. Once informed consent has been obtained, trained researchers administer a battery of assessments and upon completion of the assessments participants are randomly allocated in a 2:1 ratio to the Actissist + TAU group or the ClinTouch + TAU group. The study statistician produced a randomisation list using random permuted blocks of sizes 3 and 6. Notification of group allocation is conducted using an independent tool (eLabs; nweh.org.uk/content/elab), an online research technology platform developed and managed by The University of Manchester in order to ensure concealment of group allocation. Group allocation is revealed to the participant, clinician, baseline research assessor and project officer. Blindness of raters is ensured using a variety of procedures, including briefing participants prior to assessment not to disclose their allocation and data protection of randomisation information. The baseline RA is unblinded as they are required to conduct a training set-up session with participants on how to use the allocated app post-randomisation. Unblindings will be regularly monitored and recorded. Deliberate unblinding would only occur in the case of a serious adverse incident such as risk towards self/others by a participant.

### Data monitoring and management

Study data will be entered onto study specific SPSS (SPSS Inc., Chicago, IL, USA) database following a standard operating procedure. A separate database will be used for each time point, and this will be locked once all participants have been entered. All data will be collected on paper case report forms (CRF) that are anonymised and stored at The University of Manchester in locked filing cabinets separate from identifying information. Data will be entered by researchers electronically into the SPSS database. A random subset of data will be checked for quality control by independently checking the paper CRFs and electronically entered data and any errors will be corrected. Only the lead investigators, trial statistician and researchers will have access to the final dataset. If any participant withdraws from intervention, we will seek their permission to collect outcome data. We allow a 2-week period for gathering follow-up assessment data, after which they are coded as missed and re-contacted for the next follow-up assessment point.

Serious adverse events are regularly monitored and documented by the research team and reported immediately to the chief investigator and/or a senior clinical member of the team. Any identified adverse event is then discussed with a nominated senior clinical academic independent to the University of Manchester and the research team and an appropriate course of action is agreed and implemented.

### Participant reimbursement

Some participants in the Actissist and ClinTouch conditions will choose to borrow a smartphone from the researchers, which will be pre-loaded with £10 and then topped up £10 remotely each month to support data connectivity to last the duration of the study. To compensate for their time and contribution, all participants will be reimbursed £20 for completing each assessment time point. In order to ensure that we are covering the data usage costs associated with a participant using their own handset, we will remunerate participants with £10 every month (total of £30), if such costs are incurred. A £10 shopping voucher per fortnight will be given to participants over the intervention period who complete at least onethird of data entry points.

### Privacy and confidentiality

Maintaining service user and clinician trust when using technology is paramount and requires careful consideration when developing technology-based studies. We do not store any identifying data on either the app or the server and, therefore, many security risks are minimised. Any study data stored on the phone by the participant will be accessible only through the Actissist app. We also recommend that service users set a passcode to access their smartphone. Uploading data to a central server in real-time enables study data to be captured and so protects against data loss should a phone be lost or stolen and removes the need for personal data storage on the device. Furthermore, three general principles of information security (confidentiality, integrity and availability) will be followed in the design and implementation of the trial. All data transmitted to and from the servers will be encrypted over https with strong ciphers as detailed in the Approved Cryptographic Algorithms Good Practice Guidelines (REDCap; [45]). Cipher Suites will be implemented in compliance with Section 6 (‘Preferred uses of cryptographic algorithms in security protocols’) of the Good Practice Guidelines. In cases where participant data is downloaded from the Actissist or ClinTouch sites, this data will be securely encrypted with a pass phrase of appropriate length and complexity. Data transfers are secured by using standard web security protocols (TLS).

### Sample size

Since hypothesis testing is not the objective of this study, formal power calculations are not appropriate. In order to estimate the standard deviation of our outcome variables to inform a future sample size calculation, sample sizes between 24 and 50 have been recommended [46–48]. Our proposed sample size of 36 is within the range recommended in the literature and is sufficient for establishing feasibility and obtaining parameters to inform a robust power calculation for such a later trial.

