### Objectives

The primary objective is to determine whether in early psychosis service users a CBT-informed app (Actissist) is feasible to deliver and acceptable to use. Importantly, we will estimate parameters for the design of a future RCT, such as testing recruitment strategies, identifying a suitable primary outcome measure for use in future research, drop-out rates, proportion of eligible participants consenting, proportion continuing for 12 weeks (both arms), proportion of data-points completed across all participants, examining the characteristics of outcome measures and estimating the standard deviation and intra-cluster correlation to aid in future sample size calculation, and collecting information on follow-up response rates. Gathering such information will allow for the estimation of potential treatment effect sizes to inform a larger definitive trial as compared with service users receiving a symptom monitoring app (ClinTouch; [10]). We also aim to evaluate whether the Actissist app: (i) has the potential to impact on predictors of FEP relapse; and (ii) potentially enhances user empowerment, functioning and quality of life. In a future definitive trial, we hypothesise that Actissist will reduce the severity and distress of psychotic symptoms, perceived criticism and cannabis misuse, improve socialisation and quality of life and functioning and facilitate user-empowerment compared to the control condition at each of the follow-up time points. Using qualitative methods we will employ purposive sampling methodology to examine acceptability of the Actissist app.

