**Fig. 1 Fig1:**
[figure not shown]
Consolidated Statement of Reporting Trials (CONSORT) diagram showing design of study

Following baseline assessment, participants are randomised and informed of their group allocation. Receipt of either app will usually commence within 2 working weeks of randomisation. Blind follow-up assessments will occur at 12 weeks after baseline (post-treatment) and 22 weeks after baseline (10 weeks post-treatment). We will use both qualitative and quantitative methods to evaluate whether the aims of our study are met, ensuring that participant and staff views are adequately captured. Over a 6-month recruitment period, a total of 36 consenting EIS service users will be randomly allocated at a ratio of 2:1 to Actissist + TAU (*N* = 24) or ClinTouch + TAU (*N* = 12). Since this is a feasibility study, we aim to find out as much information as possible from service users who are allocated to and use the Actissist intervention. Therefore, we ensure that most of our service users in the study are allocated to Actissist by using a 2:1 allocation ratio.

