### Statistical analysis

Our primary analysis for a future trial would be by an intention-to-treat (ITT) approach using all randomised participants and report data in line with the Consolidated Standards of Reporting Trials (CONSORT) 2010 Statement [49] showing referral and attrition rates (i.e. participant flow). The primary analysis will involve tabulated and associated graphical summaries of the feasibility outcomes in each randomised group. To inform potential effect sizes for a future definitive trial we will use linear regression to examine the effect of random allocation on the secondary outcomes at post-treatment, adjusting for outcome measures at baseline. Presentation of the analysis will focus on point estimates and associated 95 % confidence-intervals rather than statistical significance (*P* values). Every effort will be made to follow-up all participants in both arms for assessments, and the analysis will use, where appropriate, statistical techniques for handling missing data. Although our focus will be on piloting the use of the study outcome measures, demographic information and quantitative elements of the semi-structured questionnaire will be analysed using descriptive statistics.

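### The claim that 36 participants suffice for a robust later power calculation is supported for a preliminary SD only, not for the effect size or the intra-cluster correlation

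*Protocol article*

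**What the plan says.** The Sample size section makes no power calculation, because the trial does not set out to test a hypothesis. It justifies the number by precedent. The stated purpose is "In order to estimate the standard deviation of our outcome variables to inform a future sample size calculation", and for that purpose "sample sizes between 24 and 50 have been recommended". It continues: "Our proposed sample size of 36 is within the range recommended in the literature", and concludes that this number "is sufficient for establishing feasibility and obtaining parameters to inform a robust power calculation for such a later trial".

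Other sections name further parameters that the trial is to supply. The Objectives list "estimating the standard deviation and intra-cluster correlation to aid in future sample size calculation" and add potential treatment effect sizes for a larger definitive trial. The Statistical analysis section says: "To inform potential effect sizes for a future definitive trial we will use linear regression", adjusted for the baseline value, with results shown as point estimates and 95% confidence intervals. The text under Fig. 1 fixes the design: "a total of 36 consenting EIS service users will be randomly allocated at a ratio of 2:1", that is 24 against 12.

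**The concern.** The argument moves from one parameter to three. The recommended range is introduced as a range for estimating an SD. The conclusion then covers all the parameters needed for a later power calculation and calls that calculation robust. Nothing in the article supports sufficiency for the effect size or the ICC, and no expected precision is given for any parameter.

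This is a printed claim that goes further than its own support, not a detail left to a fuller document. What is at stake is the successor trial. A team that took the claim at face value could feed in an effect estimate, a point-estimate SD or an ICC that is too imprecise to size a definitive trial.

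**Working it through.** **Inputs from the protocol article**
- Total 36, ratio 2:1, giving 24 and 12 (text under Fig. 1).
- Recommended range 24 to 50, for an SD (Sample size).
- Linear regression on allocation and baseline value, with 95% confidence intervals (Statistical analysis).
- Effect of 0.40 for CBT on the target symptom (Background), used only as a yardstick.

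**Assumptions, because the article gives no figure**
- Full follow-up, unless stated otherwise.
- Baseline-to-outcome correlation r of 0.5 or 0.7.
- 3 to 12 equal clusters and a true ICC of 0.05. The article speaks only of a number of NHS Trusts.

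**1. The plan's own figures.** 36 × 2/3 = 24, 36 × 1/3 = 12, and 36 lies between 24 and 50. These agree. There is no power or precision formula, so 36 cannot be derived further.

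**2. Effect size.** In units of the raw SD, SE = √(1/24 + 1/12) × √(1 − r²), and the half-width is t(0.975, df) × SE.
- Unadjusted, 34 df: 2.032 × 0.354 = 0.72.
- Adjusted, r = 0.5, 33 df: 2.035 × 0.354 × √0.75 = 0.62.
- Adjusted, r = 0.7, 33 df: 2.035 × 0.354 × √0.51 = 0.51.

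An observed 0.40 would have a 95% interval of 0.40 ± 0.62 = −0.22 to 1.02 at r = 0.5, and −0.32 to 1.12 unadjusted. Losses widen this. With 20 against 10 completers, the half-width is 0.69 at r = 0.5 and 0.79 unadjusted.

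**3. SD.** The 95% limits, as multiples of the estimate, are √(df/χ²). With the 33 residual df of the planned model:
- Lower: √(33/50.73) = 0.81.
- Upper: √(33/19.05) = 1.32.

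The required sample size is proportional to SD², so it varies by a factor of 33/50.73 = 0.65 to 33/19.05 = 1.73. With 34 df (unadjusted pooled SD), the limits are −19%/+31%.

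**4. ICC.** For k clusters of m = 36/k people, the one-way F interval is used. Each limit is (x − 1)/(x + m − 1), where x is the F ratio divided by F(0.975) for the lower limit or by F(0.025) for the upper limit, on k − 1 and 36 − k df. The F ratio is set at its median for a true ICC of 0.05, that is [1 + m × 0.05/0.95] × F(0.5).

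| Clusters | Typical 95% interval |
|---|---|
| 3 of 12 | −0.06 to 0.79 |
| 4 of 9 | −0.08 to 0.64 |
| 6 of 6 | −0.11 to 0.51 |
| 9 of 4 | −0.17 to 0.46 |
| 12 of 3 | −0.23 to 0.46 |

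Worked line for 12 clusters: the F ratio is 1.12; lower x = 1.12/2.586 = 0.433, giving −0.567/2.433 = −0.23; upper x = 1.12/0.3152 = 3.553, giving 2.553/5.553 = 0.46.

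**The case against.** The strongest defence is that this is a feasibility trial and behaves like one. Its primary outcomes are uptake, attrition, data completion and feedback. It disclaims hypothesis testing, calls the effect sizes potential, speaks of informing a later calculation, and commits to confidence intervals rather than P values. The imprecision will therefore be visible when results appear. No calculation in the article is wrong. All of this stands, and it limits the severity. It does not rescue the advance claim, because an interval reported afterwards does not make the number sufficient beforehand.

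A reader might infer three stronger points, none of which the article supports.
- **That 36 is the wrong number.** It lies in the cited range and is reasonable for feasibility and a preliminary SD.
- **That the definitive trial will be powered on this pilot's point estimates.** No sentence commits to that. The risk arises only if the claim is taken at face value.
- **That the future primary outcome will be the scale showing the largest difference between arms.** The Objectives do include "identifying a suitable primary outcome measure for use in future research", but they pair it with examining the characteristics of the measures, and the Statistical analysis section puts its focus on piloting them. Selection by observed effect is stated nowhere, and an article may leave the criteria to a fuller document.

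The missing definition of a cluster and the missing cluster term in the model may also be left to the analysis plan. They are not counted here. The ICC point rests on precision alone, and it holds across the range of cluster counts tried.

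**Conclusion.** The sufficiency statement claims more than the design delivers. The cited range supports a preliminary SD. Even that is known only to about −19%/+32%, so a sample size based on the point estimate varies by a factor of 0.65 to 1.73. The treatment effect has a half-width of about ±0.62 SD under the planned analysis if r = 0.5 (±0.51 at 0.7), wider than the 0.40 yardstick in either case. The ±0.72 figure applies to an unadjusted comparison, which is not the planned one. The ICC is essentially not estimated. The effect figures assume full follow-up and the stated correlations; the ICC figures assume 3 to 12 equal clusters and a true value of 0.05. Nothing in this trial's own conduct or primary analysis changes, so severity is minor to moderate.

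**What to change.** Three changes of text:
- **Sample size:** limit the word *sufficient* to feasibility and a preliminary SD. Add the expected precision with its assumptions: about −19%/+32% for the SD and about ±0.5 to ±0.6 SD for the baseline-adjusted effect with full follow-up.
- **Objectives and Statistical analysis:** state that the definitive trial's target difference will not rest on this trial's effect estimate.
- **Objectives:** delete the ICC from the parameters to be estimated, or say that it will be taken from external data.

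How the later trial allows for uncertainty in the SD can be left to its own designers. The cost is a less favourable stated property. No extra participants, assessments or analyses are needed.

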### Statistical analysis

Our primary analysis for a future trial would be by an intention-to-treat (ITT) approach using all randomised participants and report data in line with the Consolidated Standards of Reporting Trials (CONSORT) 2010 Statement [49] showing referral and attrition rates (i.e. participant flow). The primary analysis will involve tabulated and associated graphical summaries of the feasibility outcomes in each randomised group. To inform potential effect sizes for a future definitive trial we will use linear regression to examine the effect of random allocation on the secondary outcomes at post-treatment, adjusting for outcome measures at baseline. Presentation of the analysis will focus on point estimates and associated 95 % confidence-intervals rather than statistical significance (*P* values). Every effort will be made to follow-up all participants in both arms for assessments, and the analysis will use, where appropriate, statistical techniques for handling missing data. Although our focus will be on piloting the use of the study outcome measures, demographic information and quantitative elements of the semi-structured questionnaire will be analysed using descriptive statistics.

### Semi-structured interviews and qualitative analysis

At the end of the trial, a qualitative study will be undertaken to assess the acceptability of Actissist. A purposive sample will be drawn from study participants to ensure maximum variation of sample and to elicit a broad range of views regarding the acceptability of the Actissist app. This will include a balance of participants who have had a good outcome, those who have dropped out of the intervention or who refused participation, and control participants. Interviews will explore participants’ experiences and expectations of the app, participants’ views on the content, duration and intensity of the app (particularly focusing on perceptions of usefulness, engagement with the technology and facilitators/barriers to implementation), the role of an app like Actissist within the management of mental health problems, perceived benefits of the app, disappointments/concerns and ongoing support needs. All interviews will be digitally-recorded, transcribed, checked for accuracy and analysed using thematic content analysis within a qualitative methodological framework [50]. Interviews will be carried out until data saturation is complete. We will ask participants, as well as our expert reference group, to review and verify themes, usually referred to as ‘member checking’ or ‘participant verification’. Additionally, the clinical members of our research team will rigorously review the research process. This peer verification process (together with member checking) is a recognised method of ensuring trustworthiness of the data and subsequent findings [51]. Records of field notes will be maintained and reflections providing adjunctive data will be used to illuminate and justify interpretative decisions. NVivo [52] qualitative software package (QSR International Ltd., Daresbury, UK) will be used to support data management and analysis.

## Discussion

The protocol detailed above is designed to test the feasibility, acceptability and proof of concept of a smartphone app intervention for early psychosis. Digital technology has the potential to transform mental health care. To the best of our knowledge, there are no RCTs of smartphone apps delivering a psychological intervention for early psychosis. For young people in particular (‘digital natives’), it is important to develop technology-based approaches as a way of connecting with individuals about mental health issues; young people can be reluctant to seek professional help for various reasons, including stigma, embarrassment and poor recognition of symptoms. The lack of access to psychological therapies for psychosis stresses the importance of considering innovative methods and solutions to deliver support to people in need in a timely manner. We envisage Actissist as a reusable platform capable of delivering interventions for many problems. As such, we see Actissist as serving not only a clinical need but also a product development need for a platform technology to deliver self-management for a wide range of psychological disorders.

Mobile, wearable and ubiquitous technologies are advancing at an unprecedented rate. Therefore, a major research challenge is being able to rigorously evaluate mobile health (mHealth) interventions using robust scientific methods, such as RCTs, appropriately. One possible way to evaluate mHealth interventions is to adopt more sophisticated trial methodology. In standard RCTs, the intervention is fixed at the onset of the trial and is not permitted to evolve during the trial duration. Indeed, for many drugs under investigation or complex interventions, this is reasonable. However, for digital interventions, this is problematic due to the pace of change in such interventions; fixing the intervention at trial onset can render it obsolete by the time the trial results are available. Apps can also be costly and can time consuming to develop, such that the app might be out-dated by the time it is completed. Therefore, ideally, trials of digital interventions need to be adapted to allow the intervention, and potentially the control arm, to evolve as the trial progresses. Another anticipated challenge in the mHealth field is that low-income individuals may not be able to afford smartphones or indeed the sufficient levels of data necessary to run apps and other smartphone functions. To overcome this potential problem, we provide participants with mobile phone handsets and cover data network charges. However, factors such as these could be a practical barrier to continuous mHealth services. From a psychological perspective, therapeutic alliance is a key predictor of outcomes in psychological therapy [53]. Mobile technology has been criticised for lacking this essential therapeutic ingredient. Nonetheless, there is an emerging literature regarding the concept of therapeutic alliance in the context of electronic health (eHealth) and mHealth ranging from alliance service users may form with any therapist supporting the technology to ‘relationships’ that service users may form with mobile devices or apps themselves [54]. We propose to contribute to this emerging literature by developing a measure of alliance to the Actissist app and determining the feasibility of administering the new measure. Furthermore, if trials such as Actissist are effective, a major challenge is for mental health services to recognise and incorporate digital interventions into mainstream health service delivery. Indeed, compatibility issues could pose significant barriers to real-world implementation due to the fast paced development in mobile technology and platforms. One possibility for future research following this trial would be to run a pragmatic trial of the Actissist intervention in routine mental health services. Importantly, the current study has had strong user and clinician involvement from the ground up: we see service users as essential co-designers of mobile mental health interventions and essential co-investigators in trials. In sum, we believe Actissist is an important example of experimental medicine; it is a novel intervention developed from an empirically-derived theoretical framework. This study represents an important and significant step towards developing a technology platform for delivering a range of psychosocial interventions for serious mental health problems.
